### Eligibility criteria

#### Australian sample

Participants are eligible to be included in the prospective studies (cohort A and C) if the following criteria apply: (1) have a diagnosis of CP and gross motor function classified at GMFCS levels III–V; (2) aged between 4.00 and 9.99 years of age at the time of recruitment (any age less than 18.00 years for cohort C); (3) have a parent or legal guardian that is capable of giving signed, informed consent.

Participants will be excluded if the parent/legal guardians’ English language skills are not sufficient to understand the study information, provide informed consent and/or complete the parent-reported study questionnaires.

For study B (cohort B), data extracted from the NSW/ACT CPR will allow records for individuals with CP (GMFCS I–V), aged less than 18 years to be matched in data linkage. The CPR is a population-based database registry with multiple ascertainment strategies of individuals with CP who were born or live in NSW or ACT.

#### New Zealand sample

Participants are eligible to be included in the prospective studies (cohort A) if the following criteria apply: (1) have a diagnosis of CP and gross motor function classified at GMFCS levels III–V; (2) aged between 4.00 and 9.99 years of age at the time of recruitment. For study B (cohort B), data extracted from the New Zealand Cerebral Palsy Register will be linked to fracture claims data in the Accident Compensation Corporation database for children with CP (GMFCS I–V) aged less than 18 years.

##### Outcomes

For cohort groups (A, B and C) the following *retrospective early life data* will be collected at one timepoint only (baseline, T1):

I. Where available, clinical history will be retrieved from medical records, participating registries, clinical trial and neonatal discharge summaries including: sex, ethnicity, gestational age at birth, birth weight, delivery, singleton or one of multiple births, perinatal risk factors (genetic history, infection) and MRI brain findings.

II. Age and severity of CP information will include: age at CP diagnosis, GMFCS,^83^ Manual Ability Classification System (MACS),^84^ Communication Function Classification System (CFCS)^85^ and the Eating and Drinking Assessment Classification System (EDACS).^86^

III. Parent-reported early intensive therapy interventions will include: (1) age at commencement (2), the frequency and duration (dose) and (3) mode (cohort A, C)

IV. Investigations will include: X-rays of hip and/or spine, biochemistry including 25-hydroxy vitamin D (250HD) and alkaline phosphatase (cohort A, C).

Prospective longitudinal study outcomes for cohort A and C, except for DXA scans, will be measured at baseline (T1, year 1), 12 months postbaseline (T2, year 2), 2 years postbaseline (T3, year 3) and 3 years postbaseline (T4, year 4). The AusCP MSK schedule of assessments for all cohort studies (A, B, C) is outlined in table 1.

**Table 1 T1:** Data pooling plan for AusCP MSK studies

Retrospective study cohort A at 1–5 years/cohort B at fracture			Prospective follow-up from 4 to 9 yearsCohorts A and C		
Domain/test	**A**	**B**	TEST	**A**	**C**
**Child primary outcomes**					
1.Hip displacement (MP, AI)	✓		Hip displacement (MP, AI);	✓	✓
Scoliosis: PA/AP and lateral	✓		Scoliosis PA/AP and Lateral	✓	✓
DXA, pQCT			DXA, pQCT	✓	✓
Motor function: GMFM/GMFCS,	✓	✓	Motor function: GMFM/ GMFCS/MACS/CFCS.	✓	✓
Musculoskeletal: ROM assessment (lower limb and spine) including motor type/distribution.	✓		Musculoskeletal: ROM assessment (lower limb and spine) including motor type/distribution	✓	✓
Fractures: hospital admission, emergency department presentation or outpatient visit	✓	✓			
**Child secondary measures are:**					
Function: PEDI-CAT	✓		Function: PEDI-CAT	✓	
Habitual physical activity (5 day)	✓		HPA/sedentary (7 day)	✓	
Growth height/weight/BIA	✓		Growth/growth velocity: Ht/Wt	✓	✓
Skeletal fragility: # history, Pain Q	✓		Skeletal fragility: # history, PPP	✓	✓
Nutrition: 3 day diet, Feeding Q			Feeding Q, Vit D,	✓	✓
Quality of Life—CPQOL	✓		CP CHILD/CHU9	✓	
Mat/neonatal risk	✓	✓	Medical Dx CP, genomics	✓	✓
Neonatal MRI Kiddokoro (aim 2)	✓		Fiori brain lesion severity	✓	
HRU: medical/AH costs	✓	✓	HRU/medical/AH costs/PBS MBS	✓	

AI, Acetabular Index; ANZNN, Australian and New Zealand Neonatal Network; CHU9, Child Health Utility—9 Dimensions; CPCHILD, Caregiver Priorities and Child Health Index of Life with Disabilities; DXA, dual-energy X-ray absorptiometry; GMFM, Gross Motor Function Measure; HEA, Hilgenreiner’s Epiphyseal Angle; HRU, health resource utilisation; MACS, Manual Ability Classification System; MBS, Medicare Benefits Schedule; MP, migration percentage; PBS, Pharmaceutical Benefits Scheme; PEDI_CAT, Paediatric Evaluation of Disability Inventory Computerised Assessment Test; PPP, The Pediatric Pain Profile; pQCT, peripheral Quantitative Computed Tomography.

### Primary outcomes

***Hipassessment*** will involve annual AP pelvis X-rays, performed according to Hip Surveillance Guidelines for positioning children with CP.^29 30^ Reimers MP, acetabular index (AI), sphericity of femoral head, pelvic obliquity, hip abduction/adduction, femoral neck-shaft angle and Hilgenreiner’s epiphysial angle (HEA) will be analysed on all anterior–posterior pelvis X-rays. A passive range of motion (ROM) physical examination will include 12 lower limb assessments performed by the study physiotherapists. The physical examination will measure ROM^87^ of the hip (flexion, extension, abduction, rotation), knee (extension, flexion) and ankle (dorsiflexion), and this measure has demonstrated good interrater,^87 88^ intrarater^88^ and test–retest reliability^89^ in children with CP^87 88^

***Spine assessment*** will use radiological and clinical biomarkers from annual seated anterior–posterior (AP) and lateral spine X-rays (upper thoracic vertebrae to anterior superior iliac spine (ASIS)) to screen and monitor development of scoliosis. Clinical metrics evaluated on spinal X-rays including frontal Cobb angle,^90^ sagittal thoracic kyphosis angle,^90^ coronal sacral shift^91^ and shoulder height asymmetry, sagittal vertical axis,^92^ rotational spinal deformity due to axial rotation,^93^ and coronal rib vertebral angle at the apical vertebra will be utilised as a secondary proxy for rotational deformity.^94^ Clinical assessment of scoliosis will involve the Adam’s forward bend test, and CPUP assessment.^95^ Spinal symmetry will be assessed through a seated lateral flexion test and lateral functional reach test (FRT) and analysed on participants with function at GMFCS III-IV that have been identified as able to complete the test. The seated lateral flexion test involves children in a seated position with arms at their sides using lateral trunk flexion to reach their fingertips down towards the floor on each side. This measure has not been previously psychometrically evaluated in a CP child sample. This study therefore will report on the reliability and predictive validity of this measure for this population. The seated lateral FRT involves children in a seated position with their arm outstretched at a 90° angle and then using their trunk to reach as far across as possible with their arm running parallel with the floor and has high test-retest reliability.^96^ The standing version of this measure has been found to be reliable and valid in ambulant children with CP (GMFCS I – III) compared with TDC^97^ but has not been tested in those at GMFCS levels IV-V.

***Dual energy X-rayabsorptiometry(DXA)*** scans (GE-Lunar (GE Medical Systems) or Hologic [Hologic Inc, USA]) will be acquired at T1 and T3, and at T4 if a low BMD for age (Z-score<−1.5) at any site is reported at T3. Measures will include age and height matched areal BMD (aBMD; g/cm^2^), bone mineral content (BMC; grams) at proximal hip, anteroposterior (AP) lumbar spine, total body and LDF.^98^ These have been demonstrated to be reproducible in CP samples.^99^ Bone mineral apparent density (g/cm^3^) will be used to estimate volumetric BMD from the AP lumbar spine image. The total radiation exposure to provide all DXA scans at three timepoints (T1, T3 and T4) would equate to a total radiation exposure of 0.0075 mSv above normal clinical care. Changes in DXA values will be adequately determined by a baseline (T1), 24-month (T3) and 36 months (T4) assessment. The addition of a 12-month (T2) DXA reading is not expected to significantly enhance the understanding of the natural history of bone mass accrual in this cohort of children.

***TheGMFM*** is a criterion-referenced observation measure developed to measure gross motor function of children with CP.^83^ The GMFM-88 version is used to assess gross motor activities in five dimensions (lying/rolling; sitting; crawling/kneeling, standing; walking, running and jumping).

***Fracture*** sustained for any participants (retrospective and prospective) will be confirmed from patient medical records and using radiological evidence; this will be cross-referenced with an annual parent-reported fracture questionnaire. For cohort B, presentation to emergency department, outpatient clinic or admission to hospital for fracture will be identified using linked administrative health data. Data and age at presentation, procedures and length of stay will be determined.

### Classifications

***Motor type*** will be classified as: spastic, dystonic, ataxic, hypotonic, choreoathetosis, mixed or unclassifiable according to the Surveillance in Europe,^100^ and *spastic topography* as the number of limbs impaired: unilateral (hemiplegia) and bilateral distribution (diplegia, triplegia, quadriplegia) using the Australian Spasticity Assessment Scale.^101^

***Gross Motor Function Classification System (GMFCS)*** has internationally established validity, reliability and stability for the classification of children with CP, 2–12 years.^84^ As gross motor abilities change with age, separate descriptors are used for different age bands using the expanded and revised GMFCS.^102^ This classification system has demonstrated high inter-rater reliability between therapists (ICC=0.84).^103^

***MACS*** is a five-level system developed for children aged 4–18 years with good inter-rater reliability.^84 104^ The MACS classifies how well children use their hands to handle objects in day-to-day activities.^84^ This classification demonstrates high reliability between therapists (ICC=0.97) and between parent and therapist (ICC=0.96).^84^

***CFCS*** has been validated in children aged 2–18 years^85^ and classifies children’s performance in sending and receiving communicative message via their typical communication means. Good inter-rater reliability between professionals has been demonstrated for this measure (κ_w_=0.77) for children older than 4 years and high test–retest reliability 0.82.^85^

***EDACS*** classifies the eating and drinking abilities of children with CP from 3 years of age and describes the level of safety and efficiency (levels I–V) on consuming food and fluid textures.^105^ This classification demonstrates high inter-rater reliability between professionals (ICC=0.93).^86^

### Secondary outcomes

***Peripheral quantitative computer tomography (pQCT)*** of the tibia will be used to measure the volumetric BMD (mg/cm^3^), shape and size of cortical and trabecular bone, and to derive strength measures.^106^ pQCT will be performed on children GMFCS III and subset of GMFCS IV and V, from cohort A. The total radiation dose for the pQCT scans (maximum total of 3 during the study) is 0.03 mSv above normal clinical care.

***Bone biopsy (cohort C)*** will involve a transiliac bone biopsy after tetracycline labelling in 30 subjects with CP, GMFCS III-V who are undergoing scheduled hip surgery. A biopsy from the iliac crest using a 5 mm or 7.5 mm diameter trephine. Bone cellular activity and BMDD on the sample will be measured using qBEI. Measurements will be compared with normative data of BMDD established in TDC.^107^

***HPA*** will be measured using accelerometers worn on the less-affected wrist (ActiGraph GT3X+) and less-affected thigh (Axivity AX3) for 7 consecutive days immediately after each assessment visit, where day 1 is defined as the first full day after receipt of the accelerometers. Parents/caregivers will record the child’s sleep times and removal of the devices on an activity log sheet. The raw accelerometer signal will be processed into HPA outcomes using machine-learnt physical activity classification models specifically trained and validated for youth with CP who are ambulatory or use mobility aids for ambulation.^108 109^

***Brain structure*** measured via retrospective structural brain MRIs captured at any age will be assessed by study investigators at Commonwealth Scientific and Industrial Research Organisation using automated, quantitative methods, namely the developing Human Connectome Project structural pipeline^110^ or neonatal data, and the AssessCP for children aged 4–18 years.^111^ This will provide measures of brain macrostructure (regional volumes) and cortical shape (cortical thickness, sulcal depth). This data will also be assessed manually using the Fiori brain lesion severity scale,^112^ cortical thickness, sulcal depth) and to describe brain lesion characteristics. This data will be combined with clinical information to predict GMFM and musculoskeletal complications.

### Growth and nutritional status

Anthropometric measures will be performed including height, length, knee height and body weight. Body mass index (BMI) will be calculated. Nutritional status will be determined using Z-score cut-offs for height, weight and BMI for each participant, relative to Centres for Disease Control and Prevention 2000 growth data.^113^Body composition: DXA measurements of fat mass, lean body mass and BMC.^114^Feeding behaviours will be assessed through a parent report questionnaire,^113^ the Feeding Nutrition Screening Tool,^115^ the Functional Oral Intake Scale^116^ and the Australian Recommended Food Score.^117^Vitamin D and calcium intake will be collected via a parent-reported food frequency questionnaire, with consideration given to supplementation.^118^

***Pain*** variables including episodes of pain, treatment and medication will be collected using the parent-reported Paediatric Pain Profile (PPP).^119^ The PPP rates severity of pain ‘at best’ and ‘while in pain’ with good internal consistency (α=0.75–0.89) and reliability (ICC 0.74–0.89).^120^ In instances where participants can self-report pain, the Wong-Baker Faces Pain Scale will be used.^120^

***Sexual maturation*** will be measured through parent-reported pubertal status of the child via pictorial illustrations, where puberty will be defined by Tanner stage ≥2.^121^ Children with delayed or precocious puberty will have their clinical status highlighted to their treating medical team.

***Biochemistry*** will involve blood collected at each timepoint for markers of optimal growth and mineral homeostasis, including 25-hydroxy vitamin D (25OHD), calcium and alkaline phosphatase, which are altered in CP related to GMFCS, body composition, growth and nutrition.^122^

***Sun exposure***will be measured through a parent-reported 7-day sun exposure diary within 2 weeks of the 25OHD levels to record the child’s daily UV exposure,^123^ concurrent with the 7-day physical activity monitoring.

***Genetic testing*** will involve DNA from children in cohort A that will be biobanked for future use to identify potential pathogenic variants in genes implicated in CP and comorbid conditions including musculoskeletal complications. This is an optional substudy. Individuals who do not wish to participate in the genetic research may still participate in the main study. A 4 mL EDTA blood sample for DNA isolation will be collected from participants who have consented to this substudy.

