Higher prevalence of musculoskeletal risk factors for hip displacement, scoliosis, reduced BMD for age, such as Gross Motor Function Measure (GMFM), HPA/sedentary behaviour, nutritional status, body composition (fat mass/fat free mass on DXA), at 4–9 years of age will lead to poorer musculoskeletal outcomes at 8–13 years of age.The location and extent of the brain lesion(s) on structural MRI, pathophysiology of CP (motor type and distribution), motor capacity (GMFM-88) at 4–9 years of age will predict severity of musculoskeletal complications (hip displacement, scoliosis, bone fragility) and performance outcomes (Pediatric Evaluation of Disability Inventory, Computer Adapted Test, PEDI-CAT) at 8–13 years of age.The location, extent of the brain lesion(s) on semiquantitative MRI (<6 years) will predict the severity of musculoskeletal outcomes (MP>30%, Cobb>10°), at 8–13 years of age.Healthcare costs will be higher for children with greater adverse musculoskeletal biomarkers at 4–9 years of age and will lead to poorer outcomes and QoL (consequences) at 8–13 years of age.Pathologic fracture will be a major health burden in children with CP that increases with GMFCS and age.The identification of children with CP at greatest risk of fracture through a predictive tool will enable the determination of prognosis, inform therapeutic action and reduce fracture burden.Bone quality of children with moderate-to-severe CP will be abnormal compared with TDC;Genetic variation will influence onset and progression of musculoskeletal complications in CP.

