### Sample size and power calculations

The total number of participants with data in line with the primary study objectives is expected to be n=450. This assumes 4 years of data from 90% of 500 enrolled participants and is based on attrition rates in previous National Health and Medical Research Council (NHMRC) funded cohorts run by the CI team. If the HD prevalence in approximately 70% of the total cohort is assumed, the AusCP MSK study will have 90% statistical power (α=0.05) to detect absolute differences between binary risk factor categories exceeding 12%. This corresponds to detecting relative risks (RRs) falling below 0.80 or surpassing 1.24. Even when risk factors are unbalanced in a 4:1 ratio, we will be able to identify RRs of <0.74 or >1.35. For scoliosis incidence, if an overall cumulative incidence of 25% is assumed, the study will be able to detect absolute between-group differences of >11%. Note that this is an underestimate of power due to the repeated annual measurements for each child.

The bone quality cohort (C) will recruit 30 children with CP, detecting between-group differences >1.25 SD with 90% power, which are smaller differences than observed when comparing children with mild Osteogenesis Imperfecta compared with TDC.^131^

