#### Statistical analysis

Data will be stored on the research data manager hosted by lead university (The University of Queensland). To identify relationships between early biomarkers (aim 1), early brain structure (aim 2) and clinical characteristics and bone quality (aim 4) with musculoskeletal complications, we will construct multivariable regression models informed by the directed acyclic graph displayed in figure 2. The association between risk factors and primary outcomes measured on the interval scale (ie, MP%) will be investigated using mixed-effects linear regression models with child included as a random effect to account for repeated measures. Risk factor and time will be included as fixed effects, with an interaction term. Potential confounding variables will be included. For binary outcomes, mixed effects logistic regression models will be constructed and mixed effects Poisson models used for count outcomes.

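### Nutritional status, a risk factor in the first hypothesis, is defined only by Z-score cut-offs, and nothing says that the continuous Z-scores will enter the models

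*Protocol article*

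**What the plan says.** All references are to the protocol article.

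- **Aims and hypotheses.** The first hypothesis opens with "Higher prevalence of musculoskeletal risk factors for hip displacement, scoliosis, reduced BMD for age" and lists nutritional status among those factors: "HPA/sedentary behaviour, nutritional status, body composition (fat mass/fat free mass on DXA), at 4–9 years of age will lead to poorer musculoskeletal outcomes".
- **Growth and nutritional status.** The raw measures are continuous: "Anthropometric measures will be performed including height, length, knee height and body weight", with BMI calculated from them. The variable itself is then defined by cutting: "Nutritional status will be determined using Z-score cut-offs for height, weight and BMI for each participant". The reference is the CDC 2000 growth data. The section does not state the cut-off values, the number of categories or the expected share of children in each. Body composition is a separate item with no cut-off: "DXA measurements of fat mass, lean body mass and BMC".
- **Statistical analysis.** The models are described by "Risk factor and time will be included as fixed effects, with an interaction term". The form of the risk factor is not stated. Predictive models are selected by Bayesian information criteria.
- **Sample size and power calculations.** Power is given to "detect absolute differences between binary risk factor categories exceeding 12" per cent, and a 4:1 imbalance of risk factors is also considered. The analysable number is given by "The total number of participants with data in line with the primary study objectives is expected to be n=450".

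**The concern.** Z-scores have to be computed before any cut-off can be applied to them, so the study will hold the full-scale measure for every child who is measured. The article gives no analytic reason for replacing it with categories in a model. Once it is cut, children just either side of a line are treated as different, and children far apart on the same side as alike.

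The primary objective is to find early biomarkers that predict severity and progression, and the background on skeletal fragility itself lists undernutrition and low body weight among the influences on bone mass accrual. A coarsened version of that predictor has less power to show an association. It is also more easily dropped when models are chosen by an information criterion, and several categories cost further penalty terms. At stake is the test of one named risk factor and its place in the predictive model, not the validity of the study.

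**Working it through.** **The plan's own figure.** The article gives no figure for information lost by categorising. The nearest is the 12% detectable difference between binary risk factor categories. With 225 per group, 70% overall prevalence and a two-sided 5% level, the difference detectable with 90% power comes out at 13.9%, and power at 12% is 79.5%. That mismatch is a separate matter and is not used here.

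**Inputs**
- From the document: N = 450; a 4:1 split (20% against 80%), which the article uses as a general scenario and not for nutrition in particular.
- Assumed: Z-score normally distributed with SD 1; linear effect on the outcome; for the power column, an effect that has 90% power on the full scale at a two-sided 5% level.
- Assumed because not given: number and position of cut-offs, and the cohort mean Z.

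**Single cut.** With share p of children on one side of the cut and z_p the corresponding normal quantile:

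- relative efficiency RE = φ(z_p)² / [p(1 − p)]; loss = 1 − RE
- effective number = 450 × RE
- power after the cut = Φ[(1.96 + 1.2816) × √RE − 1.96]

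| Split | RE | Loss | Effective N of 450 | Power if 90% on full scale |
|---|---|---|---|---|
| 50:50 | 0.637 | 36.3% | 286 | 73% |
| 80:20 | 0.490 | 51.0% | 220 | 62% |
| 90:10 | 0.342 | 65.8% | 154 | 48% |
| 95:5 | 0.224 | 77.6% | 101 | 34% |

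Worked for 80:20: φ(−0.84)² / (0.2 × 0.8) = 0.490, so 450 × 0.490 ≈ 220, and Φ(3.2416 × 0.700 − 1.96) = Φ(0.31) ≈ 0.62.

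**Dependence on the cohort mean.** For a single cut at Z = −2 (illustrative), the loss is 86.9% if the cohort mean Z is 0 (2.3% of children below the cut), 56.1% if it is −1 (15.9% below) and 36.3% if it is −2 (half below).

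**Several ordered categories.** With category shares P_k and category means m_k (in SD units from the cohort mean), loss = 1 − Σ P_k m_k². This supposes that the categories are scored by their means. For cuts at −2, −1, 1 and 2 with mean Z = 0:

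- two outer categories: P = 0.0228, m = ±2.37
- next two: P = 0.136, m = ±1.38
- middle category: m = 0
- Σ P_k m_k² = 2 × (0.128 + 0.260) = 0.776, so the loss is 22.4%

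Over mean Z of 0, −1 and −1.5:

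| Cut-offs (illustrative) | Loss |
|---|---|
| −2, −1, 1, 2 | 18% to 22% |
| −2, −1 | 20% to 54% |
| −2, 2 | 42% to 74% |

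Across the cases examined, the loss runs from about 18% to about 87%.

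**The case against.** The strongest reply is that the cut-off sentence sits in a measurement section, while the models are specified elsewhere, and there the form of the risk factor is left open. Functional form is often left to a statistical analysis plan, which is not at hand. The sponsor may intend to use the continuous Z-scores. This stands in part: the article does not say that the Z-scores will be discarded. But it does give one definition of a variable named in a hypothesis, and that definition is categorical. The point is about a stated rule, not about missing detail.

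Four stronger readings are tempting, and the article does not support them:

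- **That nutrition enters the models as a binary variable.** The binary categories in the power statement are a generic scenario that never mentions nutrition, and the word prevalence in the first hypothesis also covers measures that have no cut-off. The definition speaks of cut-offs in the plural, which allows several ordered categories.
- **That the plan throws away 36% to 66% of the information.** That range needs one cut, normality, linearity and 10% to 50% of children on one side. The article gives none of these for nutrition. The power figures also start from an assumed 90% that it never claims for this effect.
- **That GMFM-88, physical activity and fat or lean mass are cut as well.** No cut-off is stated for any of them.
- **That categorising leaves residual confounding by nutrition.** Whether nutrition acts as confounder, mediator or exposure depends on the directed acyclic graph, which is not visible here. The plan also collects related continuous measures, including DXA body composition.

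Those related measures recover some nutritional information, but the first hypothesis lists body composition beside nutritional status as a distinct risk factor. Nor can it be said that no source supports cut-offs for this use, since the cited reference is not available.

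**Conclusion.** The point holds in a limited form. The only definition of nutritional status in the article is categorical, the variable is a risk factor in the first hypothesis, and no section says that the continuous Z-scores will be used in the models. Followed as written, the plan uses a less informative version of a measure it already has.

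The size is conditional on cut-offs that are not given: about a fifth lost with several ordered categories, a third to two thirds with one cut and 10% to 50% of children on one side, and more than 80% with a single extreme cut. These figures rest on a normal Z-score and a linear effect. If the sponsor already intends continuous terms, there is no loss and only the wording needs repair. It is worth changing because the repair is nearly free and fixes the form of the variable in the text rather than leaving it to be chosen at analysis.

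**What to change.** - In **Growth and nutritional status**, keep the Z-score cut-offs and say that they serve to describe the cohort.
- In **Statistical analysis**, state that height, weight and BMI Z-scores enter the association and predictive models as continuous terms, with a restricted cubic spline where the relation is not linear.

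The cost is one or two sentences and no new data. The small downside is one or two extra model terms where a spline is used, which the information criterion will penalise.
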